**Methods/design:**

In a single-centre, single-blinded, randomized controlled trial, we will include 140 patients aged 65-79 years with an acute displaced FNF and randomize them in a 1:1 ratio to a cemented tapered or a uncemented tapered hydroxyapatite - coated femoral stem. A cemented cup will be used in both groups. The patients will be blinded for allocation. The primary endpoints will be the incidence of all hip-related complications and health-related quality of life evaluated with EuroQol-5D (EQ-5D) index up to 2 years after surgery. Secondary outcomes will be overall mortality, general medical complications and hip function. The follow-up will be at 3 months, 1 and 2 years. Further follow-ups after end of study will be at 4 and 10 years. Results will be analysed using 95 % CI’s for the effect size. A regression model will also be used to adjust for stratification factor.

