### Randomization and blinding

The patients will be block-randomized in a 1:1 ratio, to receive either cemented or uncemented stem. We will use sealed envelopes and randomization will be stratified by sex to ensure that the sex distribution will be the same in both groups. The study subjects will be blinded to choice of treatment. To verify that the blinding is maintained during the study, the patients will be asked if they knew their assigned allocation arm at the 2-year follow-up. The surgeons and staff are not blinded during the study.

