### Outcome measurements

#### Primary endpoints

The primary endpoints will be 1) the incidence of all hip-related complications up to 2 years after surgery and 2) change in health-related quality of life assessed with EQ-5D index (EuroQol) [16] up to 2 years. Hip-related complications are defined as intra- and postoperative periprosthetic fractures, dislocation, wound infection both superficial and deep, loosening both early and late and revision of any prosthetic implant for any reason.

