### Data collection and follow-ups

The primary assessment will establish that the patient fulfils all inclusion/exclusion criteria and identify any comorbidity. The patients will then be interviewed by a research nurse regarding living conditions, mobility, activities of daily living (ADL) [22], status and health-related quality of life according to the EQ-5D during the last week before the fracture as a baseline. For all primary and secondary endpoints including ADL the patients themselves will be providing data during the study period. It is obvious that the patients’ ability to record this correctly while awaiting urgent surgery may be questioned. It is, however, impossible to collect these data in a prospective manner and the method is regularly used in patients with a fracture of the hip [1, 2, 19]. Patients who are unable or unwilling to attend follow-ups will be interviewed by telephone or they will send their answers by mail. We will use the unique Swedish personal id-number and collect data prospectively throughout the study period through a combination of a search of our databases, follow-ups and the Swedish Hip Arthroplasty Register. Non hip-related adverse events (AEs) and serious adverse events (SAEs) will be collected throughout the study period (2 years). Although the primary endpoints will be evaluated at 2 years, the study will also include a 4 and 10-year follow-up. The study visits are presented in Table 1.

**Table 1 Tab1:** All visits in the study

	d 0	d 0	0	+1 d	+4 d	5d	3 m.	1 y	2 y	4 y	10 y
	Screening	Inclusion	Randomization and surgery	POD1	POD4	End of In-pt stay	Follow-up	Follow-up	Follow-up	Follow-up	Follow-up
Screening for eligibility	x										
Informed consent		x									
Baseline data		x									
Randomization			x								
X-ray	x			x				x	x	x	x
HHS		x						x	x	x	x
VAS		x						x	x	x	x
EQ-5D		x						x	x	x	x
Adverse events			x	x		x	x	x	x	x	x
Intraoperative			x								
Blood test		x		x	x		x				

X-ray = anterioposterior and lateral radiographs, HHS = Harris hip score, EQ-5D = Quality of life score, Intraoperative = Intraoperative measurements including blood pressure, puls rate, pulse oxyometry before, during and after femoral stem insertion, VAS = Visual Analogue Scale for hip pain, Bloodtest = C-reactive protein (CRP), IL-6, Hb, D-dimer

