### Sample size and power analysis

Prior to the study start, a sample size calculation was done. To show non-inferiority with 80 % power of the primary endpoint all hip-related complications between the two groups, assuming a total complication rate of 20 %, and with a non-inferiority limit of 15 % requires 60 patients in each group. The assumed 20 % complication rate includes also minor hip-related complications as per previously published papers ranging between 10 and 20 % [1, 2, 6]. To show non-inferiority with 80 % power of the primary variable health related quality of life – HRQoL, as measured with EQ-5D requires 40 patients in each group, and with a non-inferiority limit of 0.1, assuming a value of 0.73 (SD 0.18) 1 year after the surgery [5]. The alpha (2-tailed) is set at 0.025 since we have two endpoints for the power calculation. Since this patient group has a 1-year mortality of 10 %, 70 patients in each group should be sufficient for the study.

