### Analysis

Analyses of outcome are based on the intention-to-treat principle and all patients remain in their randomized group regardless of any further surgical intervention. Patients with missing data (i.e. EQ-5D, HHS VAS etc.) at any of the follow-ups are analysed with the last observation carried forward (imputed). Descriptive statistics (means and standard deviations) will be used to describe the patient characteristics and outcome variables at the measurement points. Fisher’s exact test will be used to test the primary endpoint. We will use the Student’s *t*-test and Levene’s test for comparison of the functional outcomes with 95 % CI presented. We will use Kaplan-Meier survival curves with log-rank test for patient and hip re-operation survival analysis. The analyses will be performed with SPSS 22.0 for Mac (SPSS, Chicago, Illinois) statistical software.

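### The only listed test that fits the EQ-5D primary endpoint is an unadjusted t-test; adjusting for baseline EQ-5D and sex would gain precision at no cost, and the Abstract's adjusted regression is missing from the Analysis section

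*Protocol article*

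**What the plan says.** All places are in the protocol article.

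- **Primary endpoints:** the second primary endpoint is "change in health-related quality of life assessed with EQ-5D index (EuroQol) [16] up to 2 years".
- **Analysis:** "Fisher’s exact test will be used to test the primary endpoint". Student's t-test and Levene's test are each listed as a "test for comparison of the functional outcomes with 95 % CI presented". Apart from the survival methods, these are the only outcome tests listed. No covariate, stratum or regression model appears in the section.
- **Abstract, Methods/design:** results will be given as effect sizes with confidence intervals, and "A regression model will also be used to adjust for stratification factor".
- **Randomization and blinding:** "randomization will be stratified by sex to ensure that the sex distribution will be the same in both groups".
- **Data collection and follow-ups:** patients are interviewed about "health-related quality of life according to the EQ-5D during the last week before the fracture as a baseline".
- **Sample size and power analysis:** the EQ-5D calculation is made "with a non-inferiority limit of 0.1, assuming a value of 0.73 (SD 0.18) 1 year after the surgery", with 80% power, two-tailed alpha 0.025 and 40 patients per group. The final size is 70 per group, allowing for 10% mortality at one year.

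**The concern.** Fisher's exact test can serve only the complication endpoint, so by elimination the t-test is the comparison for EQ-5D. As written, that comparison uses neither of two variables the trial will have for every randomised patient: the baseline score as a covariate, and sex. In a non-inferiority comparison the cost falls on the width of the interval. A needlessly wide interval can cross the 0.1 limit even when the stems are truly equivalent.

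The loss could matter here because the endpoint is worded as change while the SD used for planning belongs to a follow-up value. Subtracting a weakly correlated baseline adds noise. The baseline is a pre-fracture state recalled while awaiting surgery, and the protocol itself doubts how well patients can report it. A low correlation is therefore possible, though nothing in the document establishes it.

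The reader also cannot tell from the Analysis section what role the Abstract's regression has, or whether the adjusted or the unadjusted estimate decides the EQ-5D question.

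**Working it through.** **Inputs from the protocol.** Margin 0.1; SD 0.18 (a 1-year value); two-tailed alpha 0.025, so 0.0125 on the non-inferiority side; power 80%; 70 per arm less 10% = 63 per arm. True difference taken as 0.

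**Assumptions not in the protocol.** The SD is 0.18 at baseline as well as at follow-up. The baseline/follow-up correlation r is varied from 0.2 to 0.8.

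**The plan's own figure.** n per arm = 2 × SD² × (z₁₋α + z₀.₈)² / 0.1².

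- One-sided 0.0125: 2 × 0.0324 × (2.241 + 0.842)² / 0.01 = 61.6, so 62.
- One-sided 0.025: 50.9, so 51.
- One-sided 0.05: 40.06, so 41.

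The stated 40 is approached only at one-sided 0.05, which is not the stated alpha. That is a separate matter. The comparison below therefore uses the 63 per arm expected to remain, not 40.

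**SD under each analysis.**

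- t-test on follow-up value: 0.18.
- t-test on change: 0.18 × √(2(1 − r)).
- Analysis of covariance (ANCOVA) on baseline: 0.18 × √(1 − r²).

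The ratio of ANCOVA to change-score variance is (1 − r²) / (2(1 − r)) = (1 + r)/2, which is below 1 for every r below 1. The ratio of ANCOVA to follow-up variance is 1 − r², which is below 1 for every r other than 0. The gain therefore holds whichever version of EQ-5D the t-test would be applied to.

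**Power at 63 per arm, one-sided 0.0125.** Noncentral t, with noncentrality 0.1 / (SD × √(2/63)).

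| r | SD change | SD ANCOVA | Variance ratio | Power, change | Power, ANCOVA |
|---|---|---|---|---|---|
| 0.2 | 0.228 | 0.176 | 0.60 | 58% | 82% |
| 0.3 | 0.213 | 0.172 | 0.65 | 64% | 84% |
| 0.5 | 0.180 | 0.156 | 0.75 | 80% | 91% |
| 0.6 | 0.161 | 0.144 | 0.80 | 89% | 95% |
| 0.7 | 0.139 | 0.129 | 0.85 | 96% | 98% |
| 0.8 | 0.114 | 0.108 | 0.90 | over 99% | over 99% |

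A t-test on the follow-up value has 80% power at every r.

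**Sex alone.** Share of variance explained = q(1 − q)d² / 0.18², where q is the proportion of one sex and d the sex difference in EQ-5D, both assumed. With q from 0.25 to 0.35, d of 0.03 to 0.05 gives about 0.5% to 1.8%, and d = 0.10 gives about 6% to 7%. Nearly all the gain comes from baseline.

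**The case against.** The strongest reply is that an unadjusted comparison is valid under randomisation, that ignoring stratification tends to be conservative, and that covariates are often left to an analysis plan not shown here. Validity stands. But the Analysis section does state a method, and the Abstract announces an adjusted model that this section does not carry, so there is something to reconcile in the document itself.

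Several stronger readings are tempting and are not supported:

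- **That the Abstract and the Analysis section contradict each other.** The Abstract says the regression will also be used, so it is an additional analysis. It covers only the stratification factor and lends no support to a baseline covariate.
- **That baseline is ignored.** If change is analysed, baseline enters by subtraction. The weakness is that it is not a covariate.
- **That the protocol applies the t-test to EQ-5D change in so many words.** It names functional outcomes. Extending this to EQ-5D is an inference, and only the endpoint definition says change. If follow-up values were compared, the figures below 80% would not arise, though ANCOVA would still do better (84% against 80% at r = 0.3).
- **That the stated power requires a correlation of at least 0.5.** That threshold belongs to 63 per arm. At the stated 40 per arm and the stated alpha, r = 0.5 gives 58% for the change score, and about 0.7 is needed for 80%.
- **That Levene's test distorts the error rate.** The protocol does not say the test will select the t-test variant. Even if it did, with 1:1 allocation the pooled and Welch statistics coincide at equal n. In simulation at nominal 0.025 with normal data, the two-step procedure gave 0.024 to 0.025 for SD ratios of 1 to 2 at 63 per arm.

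It is also fair that showing only low correlations would exaggerate the problem: at 0.7 and above the loss is small.

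**Conclusion.** The point holds as one of efficiency and consistency, not validity. By inference the Analysis section leaves the EQ-5D primary endpoint to an unadjusted t-test, names no baseline covariate or sex term, and omits the additional regression that the Abstract promises. Relative to a t-test on change, baseline adjustment cuts the variance by 40% at r = 0.2, 25% at r = 0.5 and 10% at r = 0.8. In power this ranges from a 24-point gain to almost nothing. Throughout the range examined the adjusted analysis stays above 80% at 63 per arm, while the change-score test falls short below r = 0.5. These sizes rest on equal SDs of 0.18 at both times, 63 evaluable patients per arm and an assumed correlation; the direction of the gain does not depend on which correlation is chosen. Adjusting for sex adds little precision, and its case is agreement with the stratified design and with the Abstract. The change is worth making, but the trial does not fail without it.

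**What to change.** In the Analysis section, name one primary EQ-5D analysis: a linear model of the 2-year EQ-5D index on arm, baseline EQ-5D and sex. Report the adjusted mean difference with its confidence interval and judge that interval against the 0.1 non-inferiority limit. With baseline in the model, using the 2-year score or the change as the response gives the same arm estimate, so this also removes the dependence on that choice.

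Keep the unadjusted comparison as supportive. State in both the Abstract and the Analysis section which estimate is primary and what role the stratification-adjusted regression has. Use the same form of model for HHS and VAS, which Table 1 also schedules at baseline. Welch or robust standard errors may replace the Levene step as a minor simplification.

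The cost is wording only. Baseline EQ-5D is already collected and sex is known at randomisation. The change should be fixed before any comparison by arm is seen, including the planned interim analysis.

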## Discussion

The strengths of the study are the patient blinding and the study design with clinically relevant outcome as the primary endpoint. The ethical committee at Karolinska Institutet has approved the study. An interim analysis on the primary endpoints will be performed when half the sample sizes in included. If there is a disproportionate number of hip-related, or other, complications in the uncemented group the study will be stopped. The results from the study will be disseminated to the medical community via presentations and publications in relevant medical journals. We believe the internal validity of this trial is good due to the strict inclusion criteria, rigorous follow-up and the blinding of the patients. Broad exclusion criterias can affect the external validity and generalizability of a study but they are mainly focusing on excluding patients with malignant disease or those with contraindications for either treatment methods as well as patients with cognitive impairment.

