## Background

Total hip replacement (THR) is the preferred method for the active and lucid elderly patient with a displaced femoral neck fracture (FNF) [1, 2]. Comparisons between cemented and uncemented stems in hip arthroplasty for patients with a FNF have almost consistently favoured cemented fixation, mainly because of greater deterioration in pain, walking ability, use of walking aids and activity of daily living [3] and because of a higher incidence of hip related complication such as periprosthetic fracture [4] for uncemented implants. Despite this, recent reports on modern, hydroxyapatite-coated femoral stems used for this patient-group have shown promising early results [5-7]. In addition, bone cement implantation syndrome (BCIS), is more prevalent in cemented than in uncemented stems [8]. It is also a commonly occurring phenomenon in patients treated for FNF with cemented arthroplasty and severe BCIS has a significant impact on early and late mortality [9]. Thus, the use of uncemented stems for this patient group may still be justified.

We hypothesized that an uncemented, proximally porous and hydroxyapatite coated femoral stem used in THR for a displaced FNF would not be associated with more adverse peri- and postoperative hip-related complications compared with a THR using cemented stem, and that the health-related quality of life for the patients would be equivalent at 2 years.

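### The interim look is tied to inclusion although both primary endpoints are evaluated at 2 years, and its stop rule acts only on an excess in the uncemented arm

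*Protocol article*

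**What the plan says.** The Discussion of the protocol article sets the timing and content of the look: "An interim analysis on the primary endpoints will be performed when half the sample sizes in included". The Abstract says the same. The planned total is given as "we will include 140 patients aged 65-79 years", randomized 1:1, so the look falls at 70 patients, about 35 per arm.

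The Discussion then sets the consequence: "If there is a disproportionate number of hip-related, or other, complications in the uncemented group the study will be stopped". This is the only stop rule in the article, and it has no counterpart for an excess in the cemented group.

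The section on primary endpoints defines the first as "the incidence of all hip-related complications up to 2 years after surgery" and the second as "change in health-related quality of life assessed with EQ-5D index (EuroQol) [16] up to 2 years". The section on data collection confirms the time point: "Although the primary endpoints will be evaluated at 2 years, the study will also include a 4 and 10-year follow-up". Table 1 marks EQ-5D at inclusion and at 1, 2, 4 and 10 years, but not at 3 months. It marks adverse events from surgery onward, including the 3-month visit.

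The Background states that bone cement implantation syndrome (BCIS) is more common with cemented than uncemented stems, and that "severe BCIS has a significant impact on early and late mortality". Overall mortality and general medical complications are recorded in both arms (Secondary endpoints).

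**The concern.** Two parts of the plan do not fit together.

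First, the trigger is inclusion, but the analysis is meant to be of endpoints that need 2 years of follow-up. The 70th patient has had no follow-up when the look falls due. A comparison of the two primary endpoints at that moment would rest on partial follow-up for complications and on few or no 2-year EQ-5D values.

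Second, the rule commits the trial to stop for harm in one arm only. The protocol's own case for studying uncemented stems includes a cement-related harm that affects mortality. The data to detect an excess of deaths or complications in the cemented arm will be collected, but no written rule acts on them.

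At stake are the safety of participants in the cemented arm and the clarity of what the look may conclude. A stop at 70 patients would also leave the non-inferiority question unanswered.

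**Working it through.** **Step 1. Size at the look.** The sample size section asks for 60 per group and allows for 10% one-year mortality: 60 / (1 − 0.10) = 66.7, so 67, consistent with the stated 70 per group. Then 2 × 70 = 140, half is 70, or about 35 per arm. Whether 60 follows from its own inputs is a separate question and does not enter here.

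**Step 2. How long accrual can last.** The trial runs from 2009 to 2025 and includes a 10-year visit. Counting 2025 − 2009 = 16 years leaves 16 − 10 = 6 years for accrual. Using both calendar years in full gives 17 − 10 = 7. The accrual rate is not stated, so I assume uniform accrual over A years and vary A from 3 to 7.

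**Step 3. Follow-up reached at the look.** The look falls at A/2 years. The number of the first 70 with at least f years since inclusion is

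70 × max(0, (A/2 − f) / (A/2)).

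For A = 6, the look is at 3 years: 70 × (3 − 2)/3 = 23.3 at 2 years, 70 × (3 − 1)/3 = 46.7 at 1 year, and 70 × (3 − 0.25)/3 = 64.2 at 3 months.

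| Accrual A (years) | Reached 2 years | Reached 1 year | Reached 3 months |
|---|---|---|---|
| 3 | 0 | 23 | 58 |
| 4 | 0 | 35 | 61 |
| 5 | 14 | 42 | 63 |
| 6 | 23 | 47 | 64 |
| 7 | 30 | 50 | 65 |

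These counts ignore deaths and missed visits. The 2-year endpoints are therefore incomplete for at least 40 of the 70 and possibly for all of them. Between 70 − 50 = 20 and 70 − 23 = 47 patients would have no scheduled EQ-5D after baseline. Most would have passed 3 months.

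**Step 4. Direction of the rule.** Let X_u and X_c be independent binomial counts with 35 patients per arm. Take a true cemented rate of 35% and an uncemented rate of 20%; the gap is the plan's assumed 20% plus its 15-point margin. Exact summation gives:

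- any uncemented excess, P(X_u > X_c): 5.9%
- uncemented lead of 3 or more: 1.8%
- uncemented excess with two-sided Fisher p < 0.05: 0.01%

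On any of these readings a true cemented excess leads to no stop, and the rare stop that occurs would be in the wrong direction.

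**Step 5. What a defined criterion would deliver.** The Analysis section names Fisher's exact test for the primary endpoint, so I use it as an illustration. The stop probability is the sum of Bin(u; 35, p_u) × Bin(c; 35, p_c) over all u > c whose two-sided Fisher p-value is below the level.

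| True rates (uncemented vs cemented) | p < 0.05 | p < 0.025 |
|---|---|---|
| 20% vs 20% | 1.3% | 0.6% |
| 10% vs 10% | 0.65% | 0.4% |
| 35% vs 20% | 21% | 14% |

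By symmetry, the same test applied to either arm has twice the false-stop chance at equal rates (2 × 1.26% = 2.5% at 20% and p < 0.05). It would then stop for a cemented excess of 35% versus 20% in 21% of trials. The 20% rate is the plan's assumption for the whole endpoint. Rates by 3 months are not given and would be lower, so power at the look could be lower too.

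**The case against.** The best defence is that the asymmetry is deliberate. The uncemented stem is the option under challenge, and the Background says that earlier comparisons mostly favoured cement. A guard on that arm is ordinary, 'disproportionate' implies a comparison with the cemented arm, and events are recorded in both. All of this stands as a reason to have the guard. It does not explain the absence of any rule for the cemented arm when the same Background names a cement-related mortality risk. The gap is in the written stop rule, not in data collection.

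Several stronger readings are tempting but not supported:

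- **That the endpoints hardly exist at the look.** The definition begins "Hip-related complications are defined as intra- and postoperative periprosthetic fractures, dislocation, wound infection both superficial and deep", so events accrue from surgery onward, and most of the 70 would have passed 3 months.
- **That the missing threshold is itself the fault.** This is a journal article, and a numerical boundary may sit in a fuller document that is not shown. What can be judged is the trigger, content and direction that the article does fix.
- **That the trial would often stop by chance.** High figures depend on cut-offs the article does not contain. With the plan's own Fisher test the chance is 0.6% to 1.3% at equal 20% rates.
- **That the extra look inflates the type I error.** The only stated action is to stop for uncemented harm. That cannot make a false non-inferiority claim more likely; it can only make any such claim less likely.
- **That pre-fracture EQ-5D scores would be carried forward at the look.** The imputation rule concerns missing follow-up data. A visit not yet due is not clearly missing, and nothing says the rule is used at the interim.
- **That unblinded staff would apply the rule.** The article does not say who applies it, and it says data are blinded in the analyses.

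**Conclusion.** The point holds in two parts.

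**Timing and content.** A look at the primary endpoints triggered by inclusion would find 0 to 30 of 70 patients with 2-year data and at most 50 with a 1-year EQ-5D. The range rests on uniform accrual over 3 to 7 years. The upper limit comes from the trial's calendar window; the lower limit and the uniform pattern are assumptions. Complications would be partly visible, so the look can serve safety but not the 2-year comparison it is described as.

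**Direction.** The stop rule does not cover the harm that the protocol itself attributes to cemented stems. With the cemented arm truly worse by 15 points, an uncemented lead of 3 or more events would appear in 1.8% of trials, and no reading of the rule acts on the true excess.

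This should be corrected, but it does not undermine the final analysis or its error rate.

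**What to change.** Restate the look as a safety comparison of hip-related complications and deaths, made once the first 70 patients have completed the 3-month visit. State that it includes no EQ-5D test and no non-inferiority claim.

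Apply the stop rule to an excess in either arm. Tie 'disproportionate' to a pre-set two-sided criterion, and state its false-stop chance and its power at 35 per arm. The table in Step 5 is an example of what to report. The level is for the sponsor to choose: moving from p < 0.05 to p < 0.025 halves the false-stop chance for an uncemented excess (1.3% to 0.6%) but lowers the chance of stopping at 35% versus 20% from 21% to 14%.

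The change is protocol wording. Its cost is that the look comes about 3 months later. If recruitment continues meanwhile, 140 × 0.25 / A further patients are randomized first: about 12 with 3-year accrual and 5 with 7-year accrual.
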